### 3.5. Outcomes

The primary outcome of this study is the change in quality of life quantified using the EQ-5D questionnaire measured at 30, 60, and 90 days after randomization. The five-level version of the questionnaire will be used (EQ-5D-5L). Additionally, the measurement of quality of life specific to the 3 domains established by the previous questionnaire has been established as co-primary outcomes. The questionnaire will be electronically delivered through the mobile application or via emails for participants to self-administer, considering its psychometric properties, when reaching the aforementioned follow-up milestones of the study. If electronic delivery of the questionnaire is not possible, it can be completed during in-person visits of the study participants.

As a secondary outcome, the difference in the development of depressive symptoms during the follow-up has been established. These symptoms will be evaluated based on the Patient Health Questionnaire 9 (PHQ-9) scale [31]. This diagnostic tool consists of 9 questions assessing the level of depression in an individual. The first 8 questions accumulate a score ranging from 0 to 3 points, where higher scores suggest a higher probability of depression. The ninth question is used to determine the impact of the patient’s symptoms on their personal life. Scores equal to or greater than 10 points demonstrate good diagnostic performance, with a sensitivity of 88% (95% Confidence Interval, CI 95% 83–92%) and specificity of 85% (CI 95% 82–88%) based on a recent systematic review [32]. This scale was chosen not only for its clinical performance but also for its extensive use in various clinical settings [31,33,34] and spectrums of chronic comorbidities [35,36]. It is important to note that the questionnaire is validated for use in the Spanish language and in the Chilean population [37]. Additionally, this tool is designed to be applied without the need for a healthcare provider’s intervention [38,39], thus it can be virtually implemented through the same application within the same time frames as the EQ-5D tool. In case of a positive screening for depression using the aforementioned scale, the treating team will be notified of the result for confirmation and treatment inclusion in participant management. Also, adherence to medical appointments established by the treating team will be evaluated as a secondary outcome, defined as the proportion of in-person attendance at medical and nursing appointments during the study period.

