The participants’ health-related quality of life will also be assessed using the EuroQol Group’s EQ-5D questionnaire. This tool evaluates an individual’s perception of their health status based on well-being in five dimensions: mobility, self-care, usual activities, pain/discomfort, and anxiety/depression. Each of these dimensions is subdivided into five response levels for each question, and scores can be assigned to synthesize an individual’s quality of life. In addition to the questions for each dimension, the EQ-5D questionnaire includes a synthesis measurement represented by a visual analog scale regarding the individual’s self-perceived current health state. The scale is a 20 cm line graduated in units where the top end represents 100 points denoting the “best imaginable health state”, and the bottom end represents 0 points indicating the “worst imaginable health state”. The respondent evaluates their current health state by drawing a line from the box marked “your own health state today” to the point that best represents their health on this visual analog scale. This questionnaire was chosen for its validation for use among oncology patients [28], as well as its favorable psychometric properties and ease of use, enabling self-administration, validation in multiple languages including Spanish, and application among Chilean patients [29,30]. All these baseline measurements will be performed once during the initial study visit by the research team, taking the form of an initial clinical interview.

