### 3.6. Statistical Analysis

#### 3.6.1. Sample Size

Current literature on the potential effect of telemonitoring platforms on outcomes such as quality of life is scarce. However, based on previous reports [40,41], it has been estimated that a total of 80 participants (40 per arm) will be necessary to achieve 80% statistical power at standard significance levels (5% alpha two-tailed), assuming an intergroup difference in EQ-5D questionnaire means of 0.1 point, a symmetric standard deviation between groups of 0.35 points, a strength of linear correlation between measurements of 0.7 (r = 0.7), and 3 instances of measurement for both groups.

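### The co-primary outcomes are three unnamed domains of an instrument the protocol describes as having five, with no success rule, and the sample size covers only the EQ-5D mean

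*Protocol article*

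**What the plan says.** Section 3.5 (Outcomes) defines the primary outcome as the "change in quality of life quantified using the EQ-5D questionnaire measured at 30, 60, and 90 days after randomization" and specifies the five-level version. It then adds that "the measurement of quality of life specific to the 3 domains established by the previous questionnaire has been established as co-primary outcomes".

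Section 3.4 (Variables) says that the same instrument assesses "well-being in five dimensions: mobility, self-care, usual activities, pain/discomfort, and anxiety/depression", together with a visual analog scale.

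Section 3.6.1 (Sample Size) gives the only significance level in the article, "standard significance levels (5% alpha two-tailed", with "80% statistical power". The quantity powered is a single one: "assuming an intergroup difference in EQ-5D questionnaire means of 0.1 point" and "a symmetric standard deviation between groups of 0.35 points".

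Section 3.6.2 (Analysis Strategy) assigns a repeated measures ANOVA to the EQ-5D score. It names no test for the individual domains, no alpha split or testing order, and no rule on how many co-primary outcomes must succeed.

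**The concern.** The primary outcome set decides what the trial may claim. Here it rests on a count that conflicts with the article's own description of the questionnaire. If three domains are meant, they are not identified, and three can be picked from five in 10 ways, which leaves room for choice after the data are seen. If five are meant, the family is larger than the text says.

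The success rule matters as much as the count. If one significant result is enough, the question is family-wise error. If every outcome must be significant, which is the strict sense of co-primary, the question is joint power. The article does not say which applies, and its sample size addresses neither.

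**Working it through.** **1. The text.** Section 3.4 lists five dimensions by name. Section 3.5 refers to three domains of that questionnaire and names none. No three-domain structure appears elsewhere in the article. The primary family is therefore the score plus 3 (four outcomes) or the score plus 5 (six outcomes).

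**2. The plan's own figure.** Inputs from Section 3.6.1: difference 0.1, SD 0.35, r = 0.7, three measurements, two-sided 5%, 80% power, 40 per arm.
- For a single measurement, n per arm = 2 × [0.35 × (1.960 + 0.842) / 0.1]² = 192.3, so 193.
- With the one baseline of Section 3.4 and three follow-ups, the variance factor for change is 0.8 + 1 − 1.4 = 0.4, which gives 77 per arm. For baseline-adjusted analysis it is 0.8 − 0.49 = 0.31, which gives 60 per arm.
- A figure close to 40 (39 per arm) arises only from change with three baseline measurements: 0.8 + 0.8 − 1.4 = 0.2.

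So the 80 participants do not reproduce from the described design. That is a separate matter. Below, 80% power per outcome is granted, which favours the plan. What matters here is that the calculation concerns one outcome and one test.

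**3. Model for the family.** The article gives no correlations between dimensions, so they are assumed. The dimension test statistics are taken as normal with common correlation ρ from 0.3 to 0.7, and the score is the standardised mean of the dimensions. For any-one-suffices, all true effects are zero, each test is two-sided at 5%, and the result is the chance of at least one rejection. For all-must-succeed, each statistic has mean 1.960 + 0.842 = 2.802 (80% power each), and the result is the chance that all exceed 1.960. Results come from 1,000,000 simulated draws.

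| Family | ρ | Error if any one suffices | Power if all must succeed |
|---|---|---|---|
| Score + 3 | 0.3 | 14.5% | 56.8% |
| Score + 3 | 0.5 | 13.0% | 61.1% |
| Score + 3 | 0.7 | 11.1% | 65.8% |
| Score + 5 | 0.3 | 21.4% | 44.0% |
| Score + 5 | 0.5 | 18.4% | 51.3% |
| Score + 5 | 0.7 | 14.9% | 59.0% |

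**4. Outer bounds.** Full independence would give 1 − 0.95⁴ = 18.5% and 1 − 0.95⁶ = 26.5%. A score built from its own dimensions cannot be independent of them, so these are ceilings and not estimates. Under all-must-succeed, error cannot exceed 5% whatever the correlation.

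**5. If an adjustment exists in a document not shown.** An equal Bonferroni split gives 0.05/4 = 0.0125 or 0.05/6 = 0.0083 per test. At a sample size giving 80% at 5%, power for the score falls to Φ(2.802 − 2.498) = 62% or Φ(2.802 − 2.638) = 56%. Section 3.6.1 does not allow for this.

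**The case against.** The strongest reply is that a condensed article need not carry the multiplicity procedure, which may sit in an analysis plan that is not shown. That stands for the adjustment method and for the model used for each item. It does not cover the count of co-primary outcomes, which the article states and contradicts, or the question of which outcomes are primary and what counts as success.

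A reader might infer more than the text supports in four places:
- **That every co-primary outcome is tested at 5%.** The level appears only in the sample size section, for the EQ-5D mean. No level is attached to the domains.
- **That the error rate exceeds 5%.** This follows only if any one unadjusted result suffices. If all must succeed, it does not.
- **That ANOVA of means is applied to five-level items.** Section 3.6.2 applies it to the EQ-5D score and names no method for the items.
- **That three is simply a slip for five.** The article does not settle this. If it is a slip, the room for picking three of five disappears, but the family grows to six.

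It is also fair to say that the magnitudes depend on assumed correlations. They illustrate the size of the problem and are not properties of this plan.

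**Conclusion.** The concern holds in a limited form. The contradiction between three domains and five dimensions is certain and nothing in the article resolves it, so the primary family is undefined and no success rule accompanies it. The error rate is undetermined, not shown to be wrong.

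Under the stated assumptions (ρ from 0.3 to 0.7, score equal to the mean of the dimensions), letting any one outcome count at an unadjusted 5% gives about 11-14% error for four outcomes or 15-21% for six. Requiring all to succeed keeps error at or below 5% but leaves joint power of about 57-66% or 44-59%, even granting each outcome 80%. Neither of these two rules delivers both 5% error and the stated 80% power for the family. Because the conflict lies in the definition of the primary outcome, it needs correcting before unblinding.

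**What to change.** Before unblinding, amend Section 3.5 as follows.
- Make the EQ-5D-5L score, on the scale to which the 0.1-point difference in Section 3.6.1 refers, the only primary outcome, tested at two-sided 5%. This matches the outcome on which the trial was sized.
- Have the sponsor reconcile the three domains with the five dimensions of Section 3.4, and list the dimensions concerned by name.
- Move the dimensions to secondary status. If any must remain confirmatory, test them only after the score is significant, with Holm's procedure among them.

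If the co-primary structure is kept instead, the least that would cure the defect is to name the domains, state whether one or all must succeed, and redo the sample size for that rule.

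The recommended change costs wording only: no added participants, visits or data. Its downside is that the dimensions lose co-primary status. The registry entry was not available here; if it carries the same wording, it should be changed to match.

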## Abstract

Cancer, a pervasive global health challenge, necessitates chemotherapy or radiotherapy treatments for many prevalent forms. However, traditional follow-up approaches encounter limitations, exacerbated by the recent COVID-19 pandemic. Consequently, telemonitoring has emerged as a promising solution, although its clinical implementation lacks comprehensive evidence. This report depicts the methodology of a randomized trial which aims to investigate whether leveraging a smartphone app called *Contigo* for disease monitoring enhances self-reported quality of life among patients with various solid cancers compared to standard care. Secondary objectives encompass evaluating the app’s impact on depressive symptoms and assessing adherence to in-person appointments. Randomization will be performed independently using an allocation sequence that will be kept concealed from clinical investigators. Contigo offers two primary functions: monitoring cancer patients’ progress and providing educational content to assist patients in managing common clinical situations related to their disease. The study will assess outcomes such as quality of life changes and depressive symptom development using validated scales, and adherence to in-person appointments. Specific scales include the EuroQol Group’s EQ-5D questionnaire and the Patient Health Questionnaire (PHQ-9). We hypothesize that the use of Contigo will assist and empower patients receiving cancer treatment, which will translate to better quality of life scores and a reduced incidence of depressive symptoms. All analyses will be undertaken with the intention-to-treat principle by a statistician unaware of treatment allocation. This trial is registered in ClinicalTrials under the registration number NCT06086990.

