## 2. Objective

The primary objective of this study is to ascertain whether, among patients with various forms of solid cancer, the use of a smartphone application designed to facilitate disease monitoring leads to an improvement in the quality of life as reported by the patients themselves compared to standard care. As secondary objectives, we aim to determine the effects of this application on the presence of depressive symptoms and assess the level of adherence to in-person appointments established by the treating team.

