### 3.4. Variables

For each patient enrolled in the study, a baseline clinical profile will be developed, including demographic, household characterization, clinical, and neoplasia-related information. Briefly, this profile will consist of demographic data, encompassing information about gender, age, highest level of education attained, marital status (single, married, cohabiting), healthcare system affiliation (Fondo Nacional de Salud, FONASA, public healthcare; Institución de Salud Previsional, ISAPRE, private insurance; or other); household characterization data including socioeconomic level, overcrowding, availability of basic services, migratory status, and support networks; and clinical information. The latter section will comprise data on relevant medical comorbidities (diabetes mellitus, heart failure, chronic obstructive pulmonary disease, bronchial asthma, chronic liver disease, fibromyalgia, coronary artery disease, and chronic kidney disease), concurrent psychiatric conditions (depression, anxiety disorders, personality disorders), habits (alcohol consumption, substance use, or smoking), and neoplasia-related information, including the specific cancer type, date of diagnosis, stage at diagnosis based on TNM (tumor, nodes, and metastasis) classification, and therapy received.

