#### 3.6.2. Analysis Strategy

For the statistical analysis, means, medians, standard deviations, interquartile ranges, ranges, and absolute and relative frequencies will be used for descriptive analysis. Inferential analysis will employ Student’s *t*-test or the Mann–Whitney U test for comparing means based on data distribution and variances, and Fisher’s Exact Test for evaluating categorical variables. The primary outcome will be evaluated in relation to the change in EQ-5D score means associated with their corresponding standard deviations through a repeated measures analysis of variance (ANOVA). Confidence intervals at 95% will also be constructed from the standard deviations of the mean changes to estimate the magnitude of the intervention effect among these patients. Additionally, the potential association between the implemented intervention and the development of categorical outcomes will be quantified using the relative risk statistic associated with their corresponding 95% confidence intervals. Subgroup analysis has not been considered in this study.

If an imbalance in participant characteristics is detected, confounding will be controlled using multivariable linear regression analyses. Model assumptions will be assessed graphically and by an evaluation of residuals. Heteroskedasticity will be addressed using the Cook–Weisberg method. All analyses will be conducted by a statistician unaware of the participants’ treatment assignment, following the intention-to-treat principle, and using Stata v.16.0^®^ software (StataCorp LP, StataCorp LLC., College Station, TX, USA, 1996–2020).

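### The depression outcome is worded as new onset in some places and as presence in another, with no PHQ-9 among the listed baseline measures and no at-risk set, so its relative risk may mix existing and new cases

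*Protocol article*

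**What the plan says.** The protocol article describes one secondary outcome in two ways.

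- **New onset.** Section 3.5: "As a secondary outcome, the difference in the development of depressive symptoms during the follow-up has been established". The Abstract expects "a reduced incidence of depressive symptoms".
- **Presence.** Section 2 aims to "determine the effects of this application on the presence of depressive symptoms".

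For the analysis, Section 3.6.2 says that "the potential association between the implemented intervention and the development of categorical outcomes will be quantified using the relative risk statistic", with 95% confidence intervals. The only PHQ-9 cut-off in the article is 10 or more (Section 3.5). It is given as a diagnostic-performance figure and is not written out as the case definition.

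Section 3.4 itemises the baseline profile, including "concurrent psychiatric conditions (depression, anxiety disorders, personality disorders"), adds the EQ-5D, and closes with: "All these baseline measurements will be performed once during the initial study visit by the research team". PHQ-9 is not in that list. It first appears in Section 3.5, where it may be given through the app on the EQ-5D time frames. For the outcome, those time frames are 30, 60 and 90 days after randomisation. Section 3.1 excludes psychiatric illness only where it hinders use of the app.

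**The concern.** Incidence and presence are different quantities with different denominators. Incidence needs a set of patients free of the condition at entry, which requires a symptom measure at entry and a rule that uses it. The article names neither, although its entry criteria admit patients who are already depressed. A patient above the cut-off both before randomisation and at day 30 would then look the same as a patient who crossed it after randomisation.

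Two things are at stake. First, the relative risk may blend new and existing cases, and it moves toward 1 if the existing cases respond less to the app. Second, the arms are small, so they may differ by chance in the share already symptomatic, and without an entry score that difference can be neither seen nor adjusted for. The outcome is secondary, but it is part of the hypothesis in the Abstract.

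**Working it through.** The plan gives no numerical basis for the PHQ-9 outcome (the sample size in Section 3.6.1 concerns the EQ-5D only), so there is no plan figure to reproduce. The only input from the document is 40 patients per arm. All the others are assumptions, shown as ranges.

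**1. Dilution of the relative risk**

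Let p0 be the share at or above the cut-off at entry, s the share of those still positive in follow-up, and pC and pT the new-case risks in the control and app arms. If entry cases are counted and the app does not affect them:

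observed RR = [p0·s + (1 − p0)·pT] / [p0·s + (1 − p0)·pC]

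Take a true new-case RR of 0.50, so pT = pC/2.

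| pC | s | p0 = 10% | p0 = 20% | p0 = 30% |
|---|---|---|---|---|
| 20% | 100% | 0.68 | 0.78 | 0.84 |
| 20% | 70% | 0.64 | 0.73 | 0.80 |
| 30% | 100% | 0.64 | 0.73 | 0.79 |
| 30% | 70% | 0.60 | 0.68 | 0.75 |

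Example (pC = 20%, s = 100%, p0 = 20%): (0.20 + 0.80 × 0.10) / (0.20 + 0.80 × 0.20) = 0.28 / 0.36 = 0.78.

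**2. Dependence on how entry cases respond**

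Keep p0 = 20%, pC = 20% and pT = 10%, and let persistence differ between arms.

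- 70% in both arms: (0.14 + 0.08) / (0.14 + 0.16) = 0.22 / 0.30 = 0.73.
- 70% control, 50% app: (0.10 + 0.08) / (0.14 + 0.16) = 0.18 / 0.30 = 0.60.
- 70% control, 35% app (the app halves persistence too): (0.07 + 0.08) / 0.30 = 0.15 / 0.30 = 0.50, so no dilution.

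**3. Power of the yes/no comparison**

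With pC = 30%, true RR 0.50 and s = 100% in both arms:

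| p0 | All 40 per arm, entry cases counted | Entry cases removed |
|---|---|---|
| 10% | 26% | 33% (36 per arm) |
| 20% | 20% | 30% (32 per arm) |
| 30% | 15% | 27% (28 per arm) |

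In this setting, removing entry cases raises power despite the smaller denominator. Power is low either way.

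**4. Chance imbalance at entry**

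At p0 = 20%, the SD of the between-arm difference is √(2 × 0.2 × 0.8 / 40) = 0.089, or 8.9 percentage points. A gap of 10 points or more (at least 4 patients) has probability 0.26 by the normal approximation and 0.33 by the exact binomial calculation.

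**The case against.** The strongest reply is that a baseline PHQ-9 is not ruled out. Section 3.5 ties its timing to the EQ-5D, which is also taken at baseline, and the article is condensed. This stands in part: the article neither states nor excludes it. The follow-up reading is still the more natural one. The tie to the EQ-5D comes with delivery through the app, which only one arm receives and only after randomisation, whereas the baseline EQ-5D is taken at an interview visit. Even with a baseline PHQ-9, no at-risk set is defined and the wording conflict remains.

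A second reply is that depression is recorded at baseline, the EQ-5D has an anxiety/depression item, and Section 3.6.2 adjusts for detected imbalance. These help only partly. A recorded diagnosis is not a current symptom score, no use of it for this outcome is stated, and the planned adjustment is linear regression, which does not yield a relative risk.

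A reader might also infer more than the text supports:

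- *That patients depressed at entry will be counted as new cases.* No sentence says so, and under the Section 2 wording counting them would be legitimate.
- *That the relative risk is bound to shrink toward 1.* This depends on how entry cases respond, as step 2 of the working shows.
- *That the comparison is biased.* Randomisation balances entry cases on average.
- *That PHQ-9 is analysed only as yes/no.* Section 3.6.2 also lists the t-test and Mann–Whitney test, and the cut-off of 10 is not declared as the outcome definition.

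**Conclusion.** The point holds as an inconsistently defined outcome with a missing entry measure. New onset (Abstract, Section 3.5) and presence (Section 2) are not reconciled, PHQ-9 is not among the listed baseline measures, and no rule says who is at risk. Followed as listed, the schedule cannot separate new from persistent symptoms by score.

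The size is conditional. With entry prevalence of 10–30%, control new-case risk of 20–30%, persistence of 70–100% and no app effect on entry cases, a true relative risk of 0.50 would appear as about 0.60–0.84. With an equal response in entry cases it stays at 0.50. None of these inputs comes from the document. The consequences are possible attenuation and unseen chance imbalance, not systematic bias between arms. This is worth correcting, but it concerns one secondary outcome and does not touch the primary analysis.

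**What to change.** 1. In Section 3.4, add a self-completed PHQ-9 to the initial visit, before randomisation and in both arms. If it is already taken then, say so.
2. Use one term for the outcome in the Abstract, Section 2 and Section 3.5, and state the cut-off as the case definition.
3. For incidence, report the relative risk of a first score at or above the cut-off among patients below it at baseline.
4. Analyse the PHQ-9 score over 30, 60 and 90 days, adjusted for baseline PHQ-9.
5. If enrolment is complete without a baseline PHQ-9, call the outcome presence throughout, as Section 2 does, and adjust for recorded depression history.

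The cost is a few minutes of questionnaire time at an existing visit, some rewording, and a somewhat smaller denominator for the incidence analysis (32 instead of 40 per arm if 20% are positive at entry).

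### The PHQ-9 is described as nine depression questions but scored on eight, and then paired with a cut-off quoted for the nine-question scale

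*Protocol article*

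**What the plan says.** Section 3.5 (Outcomes) names the instrument for the depressive-symptoms secondary outcome: "These symptoms will be evaluated based on the Patient Health Questionnaire 9 (PHQ-9) scale". It makes four statements about that instrument in succession:

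- its content: "This diagnostic tool consists of 9 questions assessing the level of depression in an individual";
- its scoring: "The first 8 questions accumulate a score ranging from 0 to 3 points, where higher scores suggest a higher probability of depression";
- the role of the last item: "The ninth question is used to determine the impact of the patient’s symptoms on their personal life";
- its threshold: "Scores equal to or greater than 10 points demonstrate good diagnostic performance", followed by a sensitivity of 88% (95% CI 83–92%) and a specificity of 85% (95% CI 82–88%) from a cited systematic review.

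The outcome itself is given only in general terms: "the difference in the development of depressive symptoms during the follow-up has been established". The same section says that a positive screen on this scale is passed to the treating team, without repeating the cut-off. Section 3.6.2 (Analysis Strategy) plans relative risks with 95% confidence intervals for categorical outcomes and names neither the PHQ-9 nor a threshold.

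**The concern.** The first statement has all nine questions measuring depression. The second and third have eight doing so and one measuring something else. Both cannot be true of the same form. The fourth then attaches a cut-off and its accuracy to the scale by name, although the only scoring description in the article is for an eight-item sum.

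This goes beyond a detail left to a fuller document: the article gives a scoring description, and it contradicts itself. Two uses of the score are exposed. One is the secondary outcome. The abstract hypothesises a lower incidence of depressive symptoms, which suggests a yes/no endpoint, and 10 is the only cut-off offered. The other is the notification of the treating team. Section 3.5 says the questionnaire needs no healthcare provider to administer it and can be delivered through the app, so the article describes no step at which a scoring error would be noticed before that notification.

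**Working it through.** **Inputs.** Item range 0 to 3, number of scored items (eight as described, nine by the scale's name and the stated number of questions) and cut-off of 10 or more: section 3.5. Number per arm, 40: section 3.6.1 (Sample Size). The 88% and 85% come from a cited review and cannot be recomputed from the article, so there is no figure of the plan's own to reproduce here.

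**Step 1, score range.** Maximum = number of scored items × 3.
- Eight items: 8 × 3 = 24, range 0–24.
- Nine items: 9 × 3 = 27, range 0–27.
- Taken word for word, the scoring sentence puts the accumulated score itself between 0 and 3, and a cut-off of 10 could never be reached. The per-item reading is therefore used below.

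**Step 2, where the two scorings disagree at 10.** Let S be the eight-item sum and I the ninth-item score (0, 1, 2 or 3). The classifications differ when S < 10 and S + I ≥ 10.

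| Eight-item sum S | Ninth-item score I | Nine-item total |
|---|---|---|
| 7 | 3 | 10 |
| 8 | 2 | 10 |
| 8 | 3 | 11 |
| 9 | 1 | 10 |
| 9 | 2 | 11 |
| 9 | 3 | 12 |

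These six pairs are the complete list. With S of 6 or less, the largest possible total is 6 + 3 = 9, so no disagreement arises.

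**Step 3, direction.** Since I ≥ 0, S + I is never below S. Nobody can be positive on eight items and negative on nine. Every disagreement is a positive missed by the eight-item sum.

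**Step 4, weight of one patient.** 1/40 = 0.025, or 2.5 percentage points of an arm's rate. The article gives no score distribution, so the number of patients in the affected band cannot be estimated.

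**Step 5, recoverability.** If the form holds nine items scored 0 to 3 and only the sum is wrong, stored item responses allow re-scoring for the analysis. If the form holds eight such items and an impact question, a nine-item total cannot be rebuilt afterwards.

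**The case against.** The best defence is that these are loose descriptive sentences in a condensed article. The article names and cites the PHQ-9 and says it is validated in Spanish and in Chile. The scoring sentence cannot be a literal rule, since word for word it caps the score at 3. A misdescription of an instrument that is scored correctly in practice fits the text at least as well as a changed scoring rule.

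Much of this stands. A reader might infer that the outcome and the notification are being computed on the wrong score. The article does not support that: it does not show the form, the app's scoring or the analysis code. A reader might also take a score of 10 or more to be the written definition of the secondary outcome and of a positive screen. It is not; the text only implies it.

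The article also does not state that the cut-off and accuracy were derived on a nine-item sum. It ties them to the scale by name, and the scale is introduced as nine questions. That link is an assumption here. The wording of the ninth item in the published questionnaire is not in the article and plays no part in this point.

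Finally, the affected band is narrow, and the same scoring would apply to both arms, so no bias between arms is shown.

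The contradiction itself survives all of this. Whichever reading is right, the number of scored items, the range and the cut-off in section 3.5 do not fit together.

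**Conclusion.** The PHQ-9 description is wrong as written, at moderate severity. If it were followed, the range would be 0–24 instead of 0–27, and six combinations of eight-item sum and ninth-item score (nine-item totals 10–12) would change from positive to negative, with none changing the other way.

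The size rests on three assumptions: items are scored 0 to 3 each, the quoted cut-off belongs to a nine-item sum, and the text is applied literally. The effect on the secondary outcome needs a fourth, that the outcome is dichotomised at 10. If the app already scores nine items, the harm is limited to a published protocol that misdescribes one of its outcomes, which still needs correcting. The primary outcome (EQ-5D) and the sample size do not depend on this score.

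**What to change.** Rewrite the PHQ-9 description in section 3.5 so that the number of scored items, the score range, and the cut-off with its quoted accuracy all refer to the same version of the instrument. If one question is recorded but not scored, say so, and say whether it is one of the nine. If an eight-item version is intended, name it and cite accuracy for that version.

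State explicitly how the score defines the secondary outcome: a threshold crossed during follow-up, a change in score, or something else.

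Check that the app form, the email form and the scoring code match the corrected text, and that item-level responses are stored. The threshold that prompts notification of the treating team is for the investigators to reconcile with the corrected description; none is proposed here.

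The cost is a few sentences of protocol text and one check of the forms and code, with no effect on sample size or the primary analysis. The check is best done before further questionnaires are collected, because an item that was not asked cannot be recovered.
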